## Methods

### Design and sample size

This pilot study is a prospective, open, interventive, balanced, bi-centric^1^, explorative RCT. The aim is to compare CBT and ST for social anxiety disorders. According to Cocks and Torgerson [47] for two-arm pilot studies of this kind, we will recruit 32 patients; 16 patients per CBT and ST, respectively (Fig. 1). Cocks and Torgerson used a confidence interval (CI) approach to calculate pilot sample sizes for continuous outcome measures. They supposed 0.3 of a standard deviation between two groups to be worthwhile, and stated that such a study would require 350 participants (assuming 80 % power and a two-sided alpha of 5 %). For pilot studies of which the primary goal is testing of the recruitment rate, they found 32 patients (approximately 9 % of the main sample size) to be required to produce a one-sided 80 % confidence limit. Cocks and Torgerson concluded that a pilot trial with that sample size, showed an estimate larger than zero and demonstrated feasibility to recruit and retain the patients, and so forth, should move forward with the main study.

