## Hypotheses

The main focus of this paper is to answer the question of what effect sizes of ST can be expected compared to CBT, to calculate how many patients will be needed to replicate effects indicated in this study. For that purpose, we descriptively and exploratively analyze the following hypotheses.**H1: Effects for social anxiety at the end of therapy (primary endpoint).** According to the SOPHO-NET [36] and the study by Willutzki and colleagues [5], we expect both CBT and ST to demonstrate a reduction of social anxiety symptoms, and that CBT will show a major change compared to the new ST.**H2: Effects for secondary outcomes at the end of therapy (primary endpoint).** According to the SOPHO-NET [36], we expect CBT to demonstrate a major change compared to the new ST on psychological functioning, social system and interpersonal functioning, symptom adjustment, and caregiver burden.**H3: Effects 9 and 12 months after the beginning of therapy (secondary and tertiary endpoint).** According to the SOPHO-NET [36] and the study by Knekt and colleagues [4], we expect both CBT and ST to show stable effects on primary and secondary outcomes during the follow-up period.

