#### Mixed-design ANOVA

We will perform mixed-design ANOVA to identify differences between treatment conditions [95]. Factors will be group (CBT or ST) and time (baseline, 8th, 15th, 20th therapy hour, end of therapy, respectively 26th therapy hour, 9 and 12 months after the beginning of therapy). Contrasts A will compare baseline with end of therapy. Contrasts B will indicate change between end of therapy, respectively 26th therapy hour, and 9 months after the beginning of therapy. Contrasts C will indicate change between end of therapy and 12 months after the beginning of therapy. We will control for differences in the length of treatment.

Time X Group interaction effect sizes will be assessed with partial eta-squared (η^2^) for the mixed-design ANOVA. Classification of effect sizes will be: η^2^ ≥ 0.01, small effect; η^2^ ≥ 0.06, medium effect; and η^2^ ≥ 0.14, large effect. Subsequently, for significant Time X Group interactions, simple effect analyses within and between groups will be performed [96]. Between-group effect sizes will be assessed with η^2^ and Cohen’s *d*. Classification of Cohen’s *d* will be: *d* ≥0.20, small effect; *d* ≥0.50, medium effect; and *d* ≥0.80, large effect [34]. In accordance with Coe [97], we will interpret Cohen’s *d* in terms of percentiles. Within-group effect sizes will be assessed with η^2^.

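### The pilot is meant to supply the effect size for sizing the main trial, but 32 patients is justified for another goal and leaves that effect size known only to about ±0.7 SD

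*Protocol article*

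**What the plan says.** **Purpose.** The Hypotheses section gives the main focus as finding "what effect sizes of ST can be expected compared to CBT, to calculate how many patients will be needed" to replicate the effects seen. The Discussion paragraph of the Abstract repeats this (evidence for calculating the confirmatory trial's patient number), and the Pilot study section says the information for that calculation is missing.

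**Sample size.** Under Design and sample size, "we will recruit 32 patients; 16 patients per CBT and ST, respectively". The justification is a cited paper on pilot sample size that uses a confidence-interval approach for continuous outcomes. As the article reports it, "They supposed 0.3 of a standard deviation between two groups to be worthwhile", and a trial of that size needs 350 patients at 80 % power and two-sided 5 %. Then: "For pilot studies of which the primary goal is testing of the recruitment rate, they found 32 patients", about 9 % of the main sample, for a one-sided 80 % limit.

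**Analysis.** The opening of Statistical analyses plans confidence intervals and between-group comparisons of the primary endpoints, with no condition attached. The Mixed-design ANOVA section reports partial eta-squared for the interaction, also unconditionally. It then says that "for significant Time X Group interactions, simple effect analyses within and between groups will be performed". The next sentence names eta-squared and Cohen's d as between-group effect sizes, without saying whether the condition carries over.

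**The concern.** The number of patients and the use of the result do not match. As the article describes it, the rule behind 32 supports a decision on whether to go on to a main trial whose size is already fixed by a 0.3 SD difference. The article instead wants to derive the main trial's size from the difference the pilot observes. That needs a reasonably precise d, and no section argues that 32 patients provide one.

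Required N varies with 1/d², so moderate error in d becomes very large error in N. A pilot that overshoots by chance leads to a main trial too small to detect the real difference; one that undershoots leads to a trial nobody can run. If d were also reported only when the interaction is significant, the values that reach the planning stage would be mostly the overshoots.

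**Working it through.** **Inputs.** From Design and sample size: 16 per arm, worthwhile difference 0.3 SD, main N 350, 80 % power, two-sided 5 %, one-sided 80 % limit. The true d of 0.3 used in steps 4 to 6 is an assumption, taken as the article's own reference value.

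**1. The plan's figures.**
- Main trial: per arm 2 × (1.960 + 0.8416)² / 0.3² = 174.4, rounded up to 175, total 350. Reproduced.
- Pilot: N = 4 × (0.8416 / 0.3)² = 31.5, rounded up to 32; 32/350 = 9.1 %. Reproduced.
- Limit at 32: 0.8416 × √(4/32) = 0.298 SD. An estimate of zero would just exclude 0.3 SD at one-sided 80 %.

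**2. Precision of d at 16 per arm.** SE ≈ √(2/16) = 0.354. The 95 % half-width is 1.96 × 0.354 = 0.69 SD (0.72 SD using t on 30 df), more than twice the difference called worthwhile. A half-width of 0.3 SD would need 4 × (1.96/0.3)² = 171, or about 172 patients.

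**3. Implied main-trial N.** Main N = 4 × (1.960 + 0.8416)² / d² = 31.4 / d². CIs for d are by noncentral t.

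| Observed d | 95 % CI | N at upper limit | N at estimate | N at lower limit |
|---|---|---|---|---|
| 0.3 | -0.40 to 0.99 | 32 | 350 | none (CI includes 0) |
| 0.5 | -0.21 to 1.20 | 22 | 126 | none (CI includes 0) |

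**4. Sizing from the observed d when true d = 0.3.** In 200,000 simulated pilots, N = 31.4/d² had median about 276 and quartiles of about 101 and 1,186. A repeat with 400,000 pilots gave 101, 277 and 1,202. The true requirement is 350.

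**5. Chance of an underpowered main trial.** Power at true d = 0.3 falls below 50 % when N < 4 × (1.96/0.3)² = 171, that is, when the pilot's |d| exceeds √(31.4/171) = 0.43. The noncentral t distribution gives this a probability of 38 %; simulation gives 38 to 39 %.

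**6. If d were gated on significance.** A two-sample t-test at end of therapy serves as a proxy for the interaction test. Significance needs |d| ≥ 2.042 × 0.354 = 0.72. At true d = 0.3 about 13 % of pilots reach it, with mean |d| about 0.92 among them, roughly three times the truth. Sizing on 0.92 gives 31.4/0.92² = 37.1, or 38 patients. On change scores, with an assumed baseline-to-end correlation of 0.7, power is still only about 19 %.

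**7. What the pilot estimates better.** On 30 df, the 95 % CI for the SD runs from √(30/46.98) = 0.80 to √(30/16.79) = 1.34 times the estimate. For a difference fixed in scale points, N scales with SD², so this is a factor of 0.64 to 1.79 on N. That is wide, but bounded.

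**The case against.** The article calls every analysis descriptive and explorative, and Biases and limitations says a main trial is needed before any confirmatory statement. The cited rule is a confidence-interval rule for continuous outcomes, and the 0.298 SD it reproduces is the precision of a group difference, so it is not foreign to effect sizes. The pilot will also yield a point estimate and an interval. All of this stands, and it lowers the severity. It does not remove the mismatch: the rule serves a decision to proceed at a size already fixed, whereas the stated use is to calculate that size.

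Four stronger readings may tempt a reader; the document does not support them.
- *The between-group effect is examined only after a significant interaction.* It is not. The primary-endpoint comparisons, the confidence intervals and the interaction eta-squared are all unconditional. The condition covers the simple-effect analyses, and only its reach to Cohen's d is unclear.
- *The plan's go criterion would stop a programme whose own H1 expects that* "CBT will show a major change compared to the new ST". The phrase "showed an estimate larger than zero and demonstrated feasibility to recruit and retain the patients" reports what the cited paper concluded, and no analysis section adopts it as a rule. No sign is given either. On LSAS-SR a higher score is worse, so a positive ST-minus-CBT difference would mean ST did worse.
- *Attrition invalidates the 32.* One loss moves the limit from 0.298 to 0.8416 × √(4/31) = 0.302 SD, which is trivial. The intention-to-treat set is defined on all 32.
- *The pilot should also supply a therapist ICC.* Sixteen therapists with two patients each could not estimate one usefully, and the article itself declines to examine therapist effects.

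**Conclusion.** The point holds in this form and should be fixed, though it does not undermine the conduct of the pilot. The justification for 32 patients serves a goal other than the stated one. A d known to about ±0.7 SD cannot fix a main-trial N: at an observed 0.3 the implied N runs from about 32 to unbounded. At a true d of 0.3, about 38 to 39 % of main trials sized this way would have under 50 % power.

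These figures assume all 32 analysed, a normal outcome with equal SDs, a two-arm comparison at one time point and a main trial sized on the observed d alone. The gating figures (13 %, 0.92) are a t-test stand-in for an interaction over seven assessments, and they apply only if d is in fact gated. The pilot-size paper was not available, so its rule is taken as the article describes it.

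**What to change.** (a) In the Abstract and Hypotheses, state that the main trial will be sized on a pre-set worthwhile difference, for example the 0.3 SD already cited, and not on the observed d. The pilot then supplies the outcome SD with its confidence limit, the pre-post correlation, recruitment and retention. If the difference stays in SD units, the pilot SD serves to express it in scale points; if it is fixed in points, the SD enters N directly.

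(b) In Mixed-design ANOVA, state that the end-of-therapy between-group difference and Cohen's d, each with a confidence interval, are reported for the primary outcomes whatever the interaction test shows.

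Both are changes of wording and need no extra patients or assessments. The cost is a more modest claim for the pilot.

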**Fig. 1 Fig1:**
[figure not shown]
Design, assessments and patient flow (CONSORT chart)

### Ethical consideration

CBT will be practiced at the Center for Psychological Psychotherapy (CPP), Heidelberg University, and ST at the Institute of Medical Psychology (IMP), Heidelberg University Hospital. All therapies will be recorded. The pilot study design, the measurement times and instruments are aligned with the studies of Willutzki and colleagues [5], Rakowska and the SOPHO-NET [48]. This research was approved by the Ethics Committee of the Heidelberg Medical Faculty (S-190/2014). Written informed consent will be obtained from each interested person. Staff will send the study information, informed consent and declaration about the usage of DVD records to each interested person after the initial telephone interview. The staff will be available for any questions on the telephone or face-to-face at the IMP during workdays. All interested persons will be informed about their rights to end their participation at any time without negative consequences. Confidentiality will be maintained at all levels of the pilot study by staff members, diagnosticians, therapists, supervisors and researchers. All of them have to declare bindingly that they will give no information to third persons. Additionally, we will work with identification codes for each interested person and patient. All data will be saved pseudonymized on the IMP server. This pilot trial will be conducted in accordance with the Declaration of Helsinki [49], as well as with the State Chamber of Physicians of Baden-Wuerttemberg, Germany.

### Recruitment

#### Patients

Recruitment started in 2014, with the first patient included on 18 November 2014, and we expect to complete recruitment in spring 2016. We distributed flyers and study information to doctors, psychological psychotherapists, occupational therapists, hospitals and psychosocial counseling centers in and around Heidelberg; gave public announcements in the local press, on the IMP website, information portals on clinical trials and Facebook; mailed to the Heidelberg University, the Heidelberg University Hospital and universities near Heidelberg; and we gave our flyer and study information to the outpatient centers of the CPP, IMP and the Central Institute of Mental Health in Mannheim. All patients will present themselves to the study team and no patients will be referred.

#### Therapists

Recruitment started in 2014, with the first therapists included in September, and was completed in November of the same year. A total of 16 therapists (eight CBT therapists; eight ST therapists) will be involved to conduct two therapies each. CBT therapists will be psychologists in their second to fourth year of training at the CPP. ST therapists will be third- to fourth-year trainees from the Helm Stierlin Institut (HSI), Heidelberg, and the Mannheim Society for Systemic Therapy (MAGST), Mannheim; most of them will be psychologists and educators. Due to the fact that CBT and ST have very different training structures, contents and certification procedures, we chose advanced therapists with different years of training in CBT and ST, respectively, of whom we expected best comparison regarding their training status in theory and practice.

### Study procedures

#### Screening and diagnostic process

Interested individuals will initially take part in a telephone screening assessment of the main socially anxious symptoms (SCID, social anxiety disorder). Persons meeting the inclusion criteria will then receive the LSAS-SR self-report measure and SCID screening questionnaires together with the study information, informed consent and declaration about the DVD record use by post. After signing and sending back these documents, the documentation will be checked and the LSAS-SR score will be calculated and analyzed. If all documents are signed and the interested person shows a LSAS-SR >30, then the individual will be invited to a SCID-I and -II face-to-face interview, including the assessment of the general level of functioning (Global Assessment of Functioning; GAF). These pre-SCID interviews will be rated by independent raters with respect to both primary and secondary diagnoses. After inclusion based on shared decision making by clinical experts in the bi-centric case conference, persons will be randomized. Subsequently, they will be informed whether they will be treated in the CBT or ST study arm. Individuals will then attend a social network interview. In this interview they will select a significant other (e.g. partner, family member, best friend) who will then be asked to fill in a questionnaire booklet assessing significant others' burden.

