##### Therapy (T1 to T5)

We will assess study outcomes before the start of therapy, after the 8th, 15th and 20th hour of therapy, as well as after therapy has ended. At each time of assessment, patients will participate in an online survey (UNIPARK) including study outcomes (Table 1). The assessment will be conducted at the IMP. Baseline data (T1) will be scheduled no more than 5 days before the first therapy session. Therapy process (T2 to T4) will be assessed no more than 5 days after the 8th, 15th and 20th hour of therapy. The primary endpoint (T5) will be defined by a joint patient-therapist decision to end therapy or by the end of 26 hours of therapy. All outcome variables will be assessed anew, along with in- and outpatient health care service data. A post-SCID and social network interview will also be conducted. Like the pre-SCID, the post-SCID interviews will be rated by independent raters considering primary and secondary diagnoses.

**Table 1 Tab1:** Assessment measures and application plan

Purpose	Perspective	Domain	Instrument	Screening	Baseline	8th, 15th, 20th hour of therapy	End of therapy, no later than 26th hour of therapy	9 and 12 months after beginning of therapy
					T1	T2 to T4	T5	T6 and T7
Screening	Pat	Social anxiety	LSAS-SR	X				
	Diag	Mental disorder SAD	SCID: SAD	X				
Outcome	Diag	Mental disorders	SCID I, II	X			X	
	Pat	Social anxiety	LSAS-SR	X	X	X	X	X
	Pat	Social anxiety	SIAS	X	X	X	X	X
	Pat	Social anxiety	SPS	X	X	X	X	X
	Diag	Global functioning	GAF	X	X		X	
	Pat	Depression	BDI-II	X	X	X	X	X
	Pat, Ref	General symptom severity	BSI	X	X	X	X	X
	Pat, Ref	Experience of social systems	EXIS	X	X	X	X	X
	Pat, Ref	Evaluation of social systems	EVOS	X	X	X	X	X
	Pat, Ref	Dyadic adjustment	DAS-12	X	X	X	X	X
	Pat	Interpersonal problems	IIP-32	X	X	X	X	X
	Pat, Ref	Symptom adjustment	ASS	X	X	X	X	X
	Ref	Burden	BAS		X	X	X	X
Process	Pat, T	Therapeutic alliance	SACiP			X	X	X
	Pat, T	Therapeutic relationship	SRS			X	X	X
	Pat	Therapy motivation	URICA			X	X	X
	Pat, T	Credibility	OAT		X			
Therapists	T	Common therapist factors	DPCCQ		X	X	X	X
Quality	R	Adherence and competence	STAS, CTAS-SP		X	X	X	X
Additional service	Pat	Service receipt	CSSRI-EU				X	X

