### Blinding and allegiance

#### Blinding

Patients will be informed about their assignment (no blinding, open trial), the general study aims and procedures, but not about specific hypotheses. Blinding will not be feasible since both the CPP and IMP are well known for their specific therapy orientation, and because of the focus on the external validity and generality of the pilot study to routine care [53]. Outcome assessments at all points in time will be conducted online (UNIPARK), and no blinding of assessors will be needed. Pre- and post-SCID diagnostics will be blinded and the assessors will not know the study arm in which each patient will be treated.

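### The significant other is chosen, and T1 very probably completed, after patients learn their arm, so Contrast A and the reference-person outcomes are exposed to knowledge of allocation

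*Protocol article*

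**What the plan says.** The section Screening and diagnostic process sets out the steps in order:

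- The case conference of the two centres decides on inclusion, and randomization follows.
- The arm is disclosed next: "Subsequently, they will be informed whether they will be treated in the CBT or ST study arm".
- Only after disclosure comes the appointment about the patient's social network. Of that appointment the article says: "In this interview they will select a significant other". The person named later receives the burden questionnaires.

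The section Therapy (T1 to T5) adds: "Baseline data (T1) will be scheduled no more than 5 days before the first therapy session". It also says: "At each time of assessment, patients will participate in an online survey (UNIPARK) including study outcomes". Neither statement places T1 before randomization or before disclosure of the arm.

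Table 1 labels T1 as Baseline, separate from Screening. At T1 it marks the three primary outcomes (patient-rated), the OAT credibility rating, the BAS (rated by the reference person only), and five scales rated by both patient and reference person (BSI, EXIS, EVOS, DAS-12, ASS).

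The Mixed-design ANOVA section uses this time point directly: "Contrasts A will compare baseline with end of therapy". The Blinding section makes the trial open to patients and says that assessors of the online outcomes need no blinding.

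**The concern.** In an open trial whose primary outcomes are self-reports, the patient is the assessor. A patient who has just been told the arm may answer the baseline questionnaire differently because of it. The arms are easily told apart: one is the established, insurance-funded treatment, and the other is new and not so funded. If the reaction differs between arms, part of it is booked as change during therapy.

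The reference person raises a separate problem. The Psychotherapy section makes involving the important members of the patient's social system the primary goal of ST, with invitations to sessions. The Discussion says CBT has no such intention. A patient who knows the arm therefore also knows whether the person named may be invited into therapy. If that influences the choice, H2 compares ratings from differently selected people, and no baseline adjustment repairs that.

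The stake is the pilot's main product. The Hypotheses section says the study is meant to supply effect sizes from which the main trial will be sized.

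**Working it through.** **Order of steps for the reference person.** This is explicit: randomization, disclosure, network interview, choice of person. Table 1 nevertheless marks the scales shared by patient and reference person (BSI, EXIS, EVOS, DAS-12, ASS) at Screening, when on the text's sequence no reference person has been named.

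**Order of steps for patient T1.** This is a strong inference from three points.

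1. T1 is dated back from the first session. The treatment centre and the therapist both depend on the arm, so that session is arranged after allocation, and disclosure directly follows allocation.
2. OAT is marked only at T1 and asks how successful the patient expects the treatment to be, which fits a patient who knows the treatment.
3. BAS at T1 needs a reference person, who is chosen only after disclosure.

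**What is available before randomization.** The screening LSAS-SR is posted, returned and scored before the SCID interview. Table 1 also marks SIAS, SPS and BDI-II at Screening, but the text describes only the LSAS-SR and SCID questionnaires at that stage.

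**How a shift enters the analyses.** Let δ be the true arm difference at T5, u the arm difference in T1 caused by knowing the allocation, and p the share of u still present at T5.

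- Endpoint-only comparison: δ + p·u. T1 does not appear, so its timing is irrelevant.
- Contrast A arm difference: (δ + p·u) − u = δ − (1 − p)·u.

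A shift common to both arms gives u = 0. A fully persistent one (p = 1) cancels in Contrast A. Only a differential shift that fades biases it, and with p = 0 it passes through in full.

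**The article's own figure.** Design and sample size reports, from a cited methods paper, 350 participants for 0.3 SD at two-sided 5 % and 80 % power. Per arm, 2 × (1.960 + 0.842)² / 0.3² = 174.4, rounded up to 175, so 350 in total. This reproduces. For the pilot, the one-sided 80 % half-width is 0.842 × √(2/16) = 0.298 SD, just under 0.3, which agrees with 16 per arm.

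**Sensitivity illustration.** The inputs are assumptions: true effect 0.30 SD, p = 0, outcome SD held at 1, shift u of 0.05 to 0.20 SD in either direction.

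| Assumed shift (SD) | Apparent effect (SD) | Main-trial N implied |
|---|---|---|
| 0 | 0.30 | 350 |
| 0.05 | 0.25 or 0.35 | 504 or 258 |
| 0.10 | 0.20 or 0.40 | 786 or 198 |
| 0.20 | 0.10 or 0.50 | 3140 or 126 |

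The table shows how sensitive the sizing would be. It does not estimate any bias.

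**The case against.** The strongest reply has four parts.

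**The primary comparison may not be touched.** The Statistical analyses section also plans direct between-group tests at the primary endpoint, which as described do not use T1. This stands. A reader might infer that the protection of randomization is lost, but the documents do not support that: only the change-based analyses are exposed. Nor is a baseline-adjusted regression on T1 planned, so an argument about a biased covariate would have no target.

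**Not everything at T1 is self-report.** Table 1 also marks the diagnostician-rated GAF at T1, and the text places a GAF rating in the pre-randomization interview, whose assessors are blinded. This stands. It is likewise too strong to say that everyone who leaves before the first session lacks T1. T1 can fall up to 5 days earlier, so a patient may complete it and then leave, and the screening LSAS-SR exists in any case.

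**A baseline just before therapy is defensible.** It separates change during therapy from change while waiting. Replacing T1 outright with the screening score would bring its own problems. LSAS-SR above 30 is an entry criterion, so regression to the mean would inflate within-arm change. The screening form is postal while T1 is online, and the interval between them is not given. This stands against replacement, but not against a sensitivity analysis, because regression to the mean should balance between randomized arms.

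**The choice of reference person is constrained.** The notes to Table 1 define this person as the most important of the significant others, and five of the six reference-rated scales also have patient ratings. No text shows that the choice differs by arm. This reduces the worry but does not remove it: the patient makes the selection, and BAS has no other rater.

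The article also calls itself descriptive and exploratory and lists openness as a limitation (Biases and limitations). It does not say there that baseline and the choice of rater follow disclosure.

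**Conclusion.** The point holds as an avoidable exposure. It does not demonstrate bias. That the reference person is chosen after disclosure is explicit; that patient T1 follows disclosure is very probable but inferred.

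The consequence is limited to Contrast A and the Time × Group effect for the self-reports, and to the reference-rated outcomes: BAS alone, and BSI, EXIS, EVOS, DAS-12 and ASS in part. A shift matters only if it differs between arms and does not carry through to T5. Its size and direction cannot be derived from the documents. On the assumptions stated, even a 0.10 SD shift would move a planned main trial from 350 to 786 or 198. The 0.3 SD benchmark belongs to the cited methods paper, so it should not be read as this trial's own target difference.

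This is an inexpensive improvement worth making, not a flaw that invalidates the design.

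**What to change.** **Patients still to be enrolled.** Hold the social network interview and name the reference person before the arm is disclosed. Where scheduling allows, complete the patient self-reports before disclosure too, leaving OAT after it.

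**All patients.** Repeat Contrast A for LSAS-SR with the pre-randomization screening score as a sensitivity analysis, and report the T1-minus-screening change by arm. Extend this to SIAS and SPS only if those screening scores were in fact collected. The check will be imprecise: with 16 per arm, its standard error is √(2/16) × √(2(1 − r)) SD, where r is the screening–T1 correlation. At an assumed r of 0.5 that is 0.354 SD, and it is smaller for a higher r. A null result would not exclude a shift of 0.1 SD.

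**Table 1.** Reconcile the Screening marks for the reference-person scales with the text, which names that person only later.

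**Cost.** Some network interviews will be held with people who are not then randomized. The order of steps will be mixed across the sample, since the first patient entered in November 2014 and recruitment was expected to end in spring 2016, so the reordering may reach few patients. The screening score is older than T1, postal, and subject to regression to the mean, which is expected to balance between arms. The sensitivity analysis itself needs no new data.
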